# Psilocybin-assisted therapy for severe alcohol use disorder: protocol for a double-blind, randomized, placebo-controlled, 7-month parallel-group phase II superiority trial

**DOI:** 10.1186/s12888-024-05502-y

**Published:** 2024-01-26

**Keywords:** Psilocybin-assisted therapy, Serotonergic psychedelics, Clinical trial, Severe alcohol use disorder

## Abstract

**Background:**

A significant number of individuals with alcohol use disorder remain unresponsive to currently available treatments, which calls for the development of new alternatives. In parallel, psilocybin-assisted therapy for alcohol use disorder has recently yielded promising preliminary results. Building on extant findings, the proposed study is set to evaluate the feasibility and preliminary clinical efficacy of psilocybin-assisted therapy when incorporated as an auxiliary intervention during inpatient rehabilitation for severe alcohol use disorder. Moreover, it intends to pinpoint the modifications in the two core neurocognitive systems underscored by dual-process models of addiction.

**Methods:**

In this double-blind, randomized, placebo-controlled, 7-month parallel-group phase II superiority trial, 62 participants aged 21–64 years will be enrolled to undergo psilocybin-assisted therapy as part of a 4-week inpatient rehabilitation for severe alcohol use disorder. The experimental group will receive a high dose of psilocybin (30 mg), whereas the control group will receive an active placebo dose of psilocybin (5 mg), both within the context of a brief standardized psychotherapeutic intervention drawing from key elements of acceptance and commitment therapy. The primary clinical outcome is the between-group difference regarding the change in percentage of heavy drinking days from baseline to four weeks posthospital discharge, while safety and feasibility metrics will also be reported as primary outcomes. Key secondary assessments include between-group differences in terms of changes in (1) drinking behavior parameters up to six months posthospital discharge, (2) symptoms of depression, anxiety, trauma, and global functioning, (3) neuroplasticity and key neurocognitive mechanisms associated with addiction, and (4) psychological processes and alcohol-related parameters.

**Discussion:**

The discussion outlines issues that might arise from our design.

**Trial registration:**

EudraCT 2022-002369-14 and NCT06160232.

**Supplementary Information:**

The online version contains supplementary material available at 10.1186/s12888-024-05502-y.

## Background

### Background of the proposed study

Alcohol use disorder (AUD) is a chronic, relapsing mental health disorder defined by compulsive patterns of alcohol seeking that endure despite harmful consequences, inducing clinically significant impairment [1]. AUD has an estimated global prevalence of 5%, with harmful alcohol use causing approximately 3 million deaths worldwide every year, representing 5.3% of global mortality [2]. A substantial proportion of individuals with AUD do not respond to available pharmacological and behavioral treatments: over 50% relapse within the month following alcohol cessation [3], and 70% relapse within the year [4]. This lack of effective treatment modalities underscores the urgent need for innovative therapeutic alternatives.

In parallel, the past decade has witnessed a renewed interest in psychedelic-assisted therapy (PAT). After an initial spike in clinical studies with lysergic acid diethylamide (LSD) in the 1950s and 1960s, prohibition halted all psychedelic research [5]. Following a 25-year hiatus, PAT has re-emerged as a promising treatment option for a range of mental health disorders [6]. Serotonergic psychedelics act as partial agonists of the serotonin 2A receptor (5-HT_2A_R) in the brain [7]. They include LSD, psilocybin (the principal psychoactive component in ‘magic mushrooms’), mescaline (found in certain species of cacti, such as peyote), dimethyltryptamine (DMT, the principal psychoactive compound in the ayahuasca brew), and 5-methoxy-N,N-dimethyltryptamine (5-MeO-DMT, found in various plant and animal species, such as the Sonoran desert toad) [8]. Serotonergic psychedelics induce nonordinary states of consciousness characterized by profound alterations in perception, cognition, and emotion [8]. These compounds present very low long-term toxicity [9, 10], are not associated with addiction [9, 11, 12] and have shown a favorable safety profile when used in clinical settings under therapeutic supervision [13].

Serotonergic psychedelics have demonstrated encouraging results in the treatment of AUD. A contemporary meta-analysis [14] pooled six randomized controlled trials (RCTs; *n* = 536) of PAT for severe AUD (sAUD) conducted in the 1960s. The trial conditions consisted of comparing one single dose of LSD (ranging from 3 mcg/kg: ∼ 210 mcg, to 800 mcg, with a median dose of 500 mcg) to control conditions, including a low dose of LSD (25 or 50 mcg), an alternative placebo (60 mg of d-amphetamine or ephedrine sulfate), time alone to write or treatment as usual, all with equivalent complementary treatment within trials. The meta-analysis demonstrated that participants treated with a single dose of LSD were significantly more likely than those in control conditions to show a reduction in alcohol misuse at the first reported follow-up, ranging from 1 to 12 months posttreatment, with an odds ratio of 1.96 in favor of the LSD treatment. Moreover, treatment comparison indicated a larger reduction in alcohol misuse and greater abstinence rates with LSD treatment than with commonly used AUD medication (i.e., naltrexone, acamprosate, and disulfiram) [14]. More recently, the first contemporary double-blind RCT of psilocybin-assisted therapy for AUD [15], which combined two psilocybin administration sessions with cognitive‒behavioral therapy and motivational interviewing, yielded additional promising results. At the 36-week follow-up, the group that received psilocybin exhibited both a significantly lower percentage of heavy drinking days and a significantly higher rate of abstinence than the group that received a placebo. However, as noted by the authors, the study sample exhibited a lower drinking intensity at screening than that observed in most AUD clinical trials, preventing generalization to populations with a more severe symptomatology. Interestingly, current evidence suggests that PAT might also be effective in treating major depressive disorder [16] and anxiety disorders [17], syndromes that are often comorbid with AUD [18, 19].

These findings pave the way for future research directions to fine-tune our understanding of PAT for AUD. First, experts in the field of PAT research have drawn attention to the need for trials that are more pragmatic in nature [20], i.e., that aim to investigate whether a treatment would have clinically meaningful effects when provided in real-world circumstances, as opposed to trials that are more confirmatory in nature, i.e., that focus on whether a treatment would have any effect in ideal circumstances [21]. Trials leaning toward pragmatism strive to provide the experimental intervention in the realistic conditions under which such treatment will eventually be provided and to reduce bias in participant selection to more closely represent the population that might ultimately seek the experimental treatment. Although both types of trials are necessary to investigate the safety and efficacy of a developing treatment, pragmatic trials, because they are provided closer to ‘real-world’ circumstances, give us more information regarding the feasibility of integrating said treatment within existing care. Trials integrated within real-world clinical pathways also provide access to a participant sample more realistically representing the target population, thereby enhancing the external validity of obtained results [20, 21].

Second, trials targeting the subgroup of individuals exhibiting an AUD defined as severe are necessary, as these patients present a specific profile with impaired psychosocial [22] and neurocognitive functioning [23, 24] and might consequently show a different treatment response than patients with moderate clinical phenotypes. Moreover, individuals with sAUD are particularly prone to repeated relapse [25] and exhibit more psychiatric comorbidities [26] alongside a higher risk of somatic diseases [27], warranting a prioritization in search of better treatment alternatives.

Third, while several authors have proposed diverse mechanisms of action across levels of analysis [28–31], a data-driven comprehension of the mechanisms underpinning PAT’s therapeutic efficacy in the context of AUD remains lacking.

Last, systematic unblinding has been raised as a major threat to the validity of extant findings from ‘double blind’ PAT trials due to high expectancy, presumably resulting in large placebo and nocebo effects in the experimental group and the control group, respectively [32–34]. Studies have used inactive placebos (e.g., [17, 35]), active placebos whose effects considerably differ from the acute effects of serotonergic psychedelics (e.g., [15, 36, 37]), or doses of psilocybin presumably too low to maintain blinding (e.g., [38, 39]), leading to a general call for more effective active placebo conditions and a systematic reporting of blinding efficacy [32–34].

### Psilocybin-assisted therapy for severe alcohol use disorder: potential mechanisms of action

Below, we present a nonexhaustive selection of proposed therapeutic mechanisms that our study aims to interrogate. In considering multilevel approaches, the integrative view, which aims toward integrating all levels in one comprehensive theory, contrasts with the pluralistic view, which postulates that diverse complementary pathways must be considered to achieve an exhaustive understanding of a given phenomenon [40]. Although the elegant simplicity of an overarching theory is appealing, the multifactorial nature of psychiatric disorders [41], combined with our currently limited understanding of PAT’s mode of action and the possibility that therapeutic mechanisms differ across individuals receiving treatment [40], encourages us to adopt a pluralistic approach in our proposed research.

#### Cortical neuroplasticity

Substance use disorders have been defined as ‘diseases of learning and memory’ [42], whereby drugs of abuse usurp the neural mechanisms underlying these processes by impairing neuroplasticity. This long-term dysregulation has been hypothesized to underpin the learning difficulties observed in patients with sAUD, thereby constituting a major challenge to fostering beneficial change through psychotherapy [29].

Preclinical studies suggest that serotonergic psychedelics belong to the class of psychoplastogens, i.e., compounds capable of rapidly promoting neuroplasticity in cortical neurons (see [43] for a review). It has been suggested that these properties may represent a key mechanism underlying the efficacy of serotonergic psychedelics in the treatment of psychiatric disorders [44, 45], whereby psychedelic-induced neuroplasticity may open a window of opportunity for therapeutic learning and associated beneficial behavioral change [43]. However, there is little direct evidence of psilocybin-induced cortical plasticity in humans, with no evidence in individuals with AUD, and the relationship between psychedelic-induced cortical neuroplasticity and clinical outcomes remains to be established [43].

#### Neurocognitive mechanisms: a dual-process approach

According to the Impaired Response Inhibition and Salience Attribution (I-RISA) dual-process model of addiction [46], problematic alcohol use results from a disturbed balance between 2 interacting neurocognitive systems: a strengthened striatum-dependent reward system and a weakened prefrontal cortex-dependent reflective system. As addiction develops and exposure to alcohol intensifies, successive neuroadaptations in these interconnected cerebral networks lead to overactivation of the reward system in response to alcohol-related stimuli, generating craving and an automatic approach tendency toward alcohol cues, while alcohol-induced neurotoxicity precipitates alterations in prefrontal structures involved in cognitive control, disabling the voluntary inhibition of prepotent responses and a flexible adaptation to a changing environment [47].

Preliminary preclinical evidence suggests that psychedelics’ psychoplastogenic properties [44] might directly counteract the hypofrontality observed in chronic alcohol exposure [48], thereby restoring the function of the reflective prefrontal system and its regulatory action on the reward system. Several studies established a causal role for reduced prefrontal metabotropic glutamate receptor 2 (mGluR2) function in craving and relapse responses in preclinical models of alcohol dependence [48–52]. More recently, a single administration of psilocybin was found to restore mGluR2 expression and reduce operant alcohol-seeking behaviors in alcohol-dependent rats [48]. However, to our knowledge, there are no published data to date regarding the neurobiological mechanisms associated with PAT in individuals with sAUD. Consequently, the direct influence of PAT on key functions outlined by the I-RISA dual-process model of addiction, namely, alcohol cue reactivity and inhibitory control, and their role in clinical improvement remain unknown.

#### Psychological mechanisms - role of the acute psychedelic experience

Across psychiatric diagnoses, PAT clinical trials have suggested a relationship between the quality of the acute psychedelic experience and clinical ameliorations [36, 53, 54]. Several dimensions predicted improvement, of which the majority are associated with the ‘mystical’ quality of the experience, which is characterized by feelings of unity, sacredness, ineffability, a noetic quality, transcendence of time and space, and a deeply felt positive mood [55]. Researchers have also proposed alternative putative mediators of efficacy related to the acute psychedelic effects, including operant conditioning of acceptance (‘learning to let go’ [56]) or the opportunity to access and process deep traumatic memories otherwise unbearable and/or inaccessible (the “helioscope” hypothesis [57]).

#### Psychological mechanisms - psychological flexibility

The concept of psychological flexibility, which was initially developed within the acceptance and commitment therapy (ACT) framework, is defined as ‘the ability to contact the present moment more fully as a conscious human being, and to change or persist in behavior when doing so serves valued ends’ [38, p.7]. Augmented psychological flexibility is hypothesized to facilitate reductions in alcohol abuse by enhancing one’s capacity to navigate distressing experiences without resorting to escape or avoidance while concurrently bolstering motivation to change [58]. Two retrospective survey studies suggest that increased psychological flexibility might mediate the therapeutic effects of the quality of the psychedelic experience on depression and anxiety on the one hand [59] and of psychedelic therapy on alcohol consumption and posttraumatic stress symptoms on the other hand [60]. Of note, the psychotherapeutic intervention accompanying the psilocybin session in our study will draw from key elements of ACT. The intervention and its rationale are described in the methods section.

#### Psychological mechanisms - connectedness

Increased connectedness to oneself, others, and the world has been proposed as a key psychological mechanism underlying PAT’s transdiagnostic efficacy [61–64]. In qualitative interviews, participants identified this tri-dimensional factor as a key element underlying the therapeutic effect of PAT [61, 62], including reduced craving and substance use in individuals with addiction [62].

#### Psychological mechanisms - alcohol-related parameters

The first contemporary pilot trial of PAT for AUD [54] revealed decreased craving for alcohol and both increased motivation to change alcohol consumption behavior and abstinence self-efficacy following PAT. While encouraging, these effects need to be replicated in RCTs with larger samples.

### Proposed study

Here, we present the protocol for an RCT aiming to determine the feasibility and preliminary clinical efficacy of PAT as a complementary intervention during inpatient rehabilitation for sAUD and to characterize associated changes in the two key neurocognitive systems identified by dual-process models of addiction. We strive to address the aforementioned open questions and limitations by, first, conducting a ‘pragmatic’ trial that integrates PAT within an existing model of care, i.e., the classic four-week inpatient rehabilitation program proposed in a public university hospital, to assess the feasibility and efficacy of this intervention when provided in close-to real-world circumstances; second, defining our population to only include patients with an AUD defined as severe according to the Diagnostic and Statistical Manual of Mental Disorders, Fifth Edition, Text Revision (DSM-5-TR; 6 criteria or more [65]); and, third, proposing an active placebo condition aimed at maintaining blinding, while systematically assessing and reporting blinding efficacy in participants and therapists.

Our primary hypotheses are as follows:

A greater decrease in the percentage of heavy drinking days will be observed among participants receiving a high dose of psilocybin (30 mg, high dose group) than in those receiving an active placebo (5 mg psilocybin, active placebo group) from baseline to four weeks posthospital discharge.Both treatment arms will not differ in terms of serious adverse reactions during the course of the trial.

Furthermore, our secondary clinical and mechanistic hypotheses are as follows:

The high-dose group will show a greater improvement in a range of alcohol consumption parameters than the active placebo group (↓ % of heavy drinking days at 6 months posthospital discharge, ↓ drinks per day and ↑ % of days of abstinence at 4 weeks and 6 months posthospital discharge).The high-dose group will demonstrate greater reductions in depression, anxiety, and subsyndromal trauma symptoms, as well as a greater improvement in health-related quality of life compared to the active placebo group.The high-dose group will demonstrate greater increases in psychological flexibility and connectedness than the active placebo group. These increases will correlate with clinical outcomes.The high-dose group will show a greater increase in neuroplasticity compared to the active placebo group, as measured with the EEG-derived auditory long-term potentiation (LTP) paradigm [66]. This increase will correlate with clinical outcomes.The high-dose group will show a greater improvement in alcohol-related parameters than the active placebo group (↑ abstinence self-efficacy, ↑ motivation to change, ↓ craving). These improvements will correlate with clinical outcomes.

Exploratory outcomes:

Modulations of EEG-derived measures of alcohol cue reactivity and inhibition will be compared across groups, and their relationship with clinical outcomes will be investigated.We will explore the impact of the quality of the acute psilocybin journey, in terms of experiential avoidance vs. acceptance, mystical experience, and trauma processing, on clinical outcomes.We will explore the impact of the therapeutic alliance on the quality of the psilocybin experience and on clinical outcomes.We will explore the impact of psilocybin on self-reported interoception and its associations with clinical outcomes.

Blinding and expectancy will be assessed systematically.

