### Trial population

Sixty-two participants will be included, with 31 participants receiving the experimental treatment (psilocybin high dose: 30 mg) and 31 participants receiving the active placebo (psilocybin low dose: 5 mg).

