#### Sample size

In line with extant studies indicating medium to large effects of PAT on alcohol consumption in patients with AUD (Cohen’s d = 1, [54]; Hedges’ g = 0.52 [15]), the sample size was calculated to observe a medium-size effect (Cohen’s f = 0.25) with a power of 0.9 and a type I error set at 0.05. A priori power calculation based on the primary clinical hypothesis (mixed-design analysis of variance, two groups: high dose vs. active placebo; two timepoints: % heavy drinking days from 8 weeks prehospitalization to 1 day prehospitalization vs. % heavy drinking days from hospital discharge to 4 weeks posthospital discharge) indicated a needed sample size of *n* = 46. Accounting for 25% attrition, we set the total sample size to *n* = 62. If the drop-out rate is higher, we will continue to include participants until 46 have completed visit 14 (primary clinical outcome).

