#### Primary feasibility and safety outcomes

For full transparency on feasibility, we will report on both inclusion and retention rates. A consort diagram illustrating the participant retention rate during the recruitment, screening, and data collection stages will be presented. Demographic information and reasons for exclusion will be reported.

 [100] have drawn attention to a potential underreporting of adverse events in PAT studies due to a lack of systematic assessment and disclosure. To address this limitation, safety has been added as a primary outcome in our trial. Adverse events will be systematically recorded at each study visit and follow-up and reported in trial publications. They will be classified according to severity, causality, and whether they were expected or not.

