### Data analysis

The data will be analyzed according to a statistical analysis plan that will be uploaded on ClinicalTrials.gov before unmasking. Significance levels for all analyses will be set at 0.05. Clinical outcome analyses (alcohol consumption parameters) will be performed on the intention-to-treat population, including all randomized patients who have completed the dosing session (visit 7). Changes in continuous outcomes will be analyzed with mixed-model analysis of variance with Helmert contrasts when indicated. For time series analysis, general linear mixed models will be used in the case of missing data. Mediation analyses will be used to evaluate whether hypothesized mechanistic variables mediate the effect of treatment on clinical improvements, for example, whether the mystical experience score during psilocybin administration mediates the impact of treatment on changes in the percentage of heavy drinking days. Treatment-emergent adverse events will be classified, tabulated, and treatment groups contrasted using Chi squared or Fisher’s exact test.

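### The primary safety hypothesis is that the arms will not differ in serious adverse reactions, but the only safety comparison named is a test of difference, and its non-significance cannot support that hypothesis

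*Protocol article*

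**What the plan says.** Under Proposed study, the protocol article gives two primary hypotheses. The first is greater efficacy of the high dose. The second is on safety: "Both treatment arms will not differ in terms of serious adverse reactions during the course of the trial". Under Primary feasibility and safety outcomes it adds that "safety has been added as a primary outcome in our trial", in response to concern about under-reported adverse events in this field.

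Data analysis names one between-arm safety comparison. Treatment-emergent adverse events are to be classified and tabulated, with "treatment groups contrasted using Chi squared or Fisher’s exact test". The same section states: "Significance levels for all analyses will be set at 0.05". The article gives no equivalence or non-inferiority margin for safety, and its title calls the trial a superiority trial.

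Trial population fixes the arms, "with 31 participants receiving the experimental treatment (psilocybin high dose: 30 mg) and 31 participants receiving the active placebo". The size comes from an "A priori power calculation based on the primary clinical hypothesis", that is, from efficacy. No size or precision is stated for safety.

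**The concern.** Chi-squared and Fisher's exact tests take equality of the arms as the null hypothesis and look for evidence against it. When such a test is not significant, the data are compatible with equality, but they may be equally compatible with a large difference. The test can contradict a hypothesis that the arms will not differ, but it cannot support one. Supporting it needs either a margin that the confidence interval must exclude, or a plain estimate whose interval shows which differences remain possible.

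The gap matters most when events are few, as one would expect of serious adverse reactions (an assumption, since the article gives no expected rate). The test then has little chance of reaching significance even if one arm is clearly worse, and a reader who sees a primary hypothesis of no difference beside a non-significant p-value may take it as evidence of equal safety. That would work against the article's own reason for making safety a primary outcome.

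**Working it through.** **Inputs.** 31 per arm (Trial population). Alpha 0.05 (Data analysis), taken as two-sided because sidedness is not stated. Tests: Fisher's exact or chi-squared (Data analysis), with no rule in the article for choosing between them. The event rates below are illustrative.

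**1. The plan's own figure.** Sample size asks for a "medium-size effect (Cohen’s f = 0.25) with a power of 0.9 and a type I error set at 0.05" and arrives at 46. For the group-by-time interaction with two groups and m = 2 time points, the noncentrality is λ = f² × N × m / (1 − ρ). The article does not state ρ; 0.5 is assumed. With N = 46, λ = 0.0625 × 46 × 2 / 0.5 = 11.5 and power is 0.912. N = 44 gives 0.8997, so 46 is the smallest even N that reaches 0.90. For attrition, 46 / 0.75 = 61.3, rounded up to 62. Both figures reproduce, and neither involves safety.

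**2. What each test does with 0/31 against x/31.**

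- Fisher, x = 5: p = 2 × C(31,5) / C(62,5) = 2 × 169,911 / 6,471,002 = 0.0525, not significant.
- Fisher, x = 6: p = 2 × 736,281 / 61,474,519 = 0.024, significant.
- Uncorrected chi-squared, x = 5: χ² = 62 × (31 × 5)² / (31 × 31 × 5 × 57) = 5.44, p = 0.020, significant.

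| Events (0/31 against) | Fisher p | Chi-squared p, uncorrected | Chi-squared p, Yates |
|---|---|---|---|
| 3/31 (9.7%) | 0.238 | 0.076 | 0.237 |
| 4/31 (12.9%) | 0.113 | 0.039 | 0.121 |
| 5/31 (16.1%) | 0.053 | 0.020 | 0.062 |
| 6/31 (19.4%) | 0.024 | 0.010 | 0.032 |

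The largest non-significant split is 0% against 16.1% for Fisher and Yates, and 0% against 9.7% for uncorrected chi-squared. At 0 against 5 the expected number of events is 2.5 per arm, where Fisher is the conventional choice.

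**3. Power when one arm's true rate is 0%.** Fisher then rejects only if the other arm has 6 or more events, and uncorrected chi-squared only if it has 4 or more. Power is therefore P(X ≥ 6) or P(X ≥ 4), with X binomial(31, p).

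| True rates | Fisher | Chi-squared, uncorrected |
|---|---|---|
| 0% and 5% | 0.4% | 7% |
| 0% and 10% | 8% | 38% |
| 0% and 16.1% | 38% | 76% |
| 0% and 25% | 82% | 97% |

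**4. What an interval would show.** The Newcombe 95% interval for the risk difference combines the Wilson limits of each arm.

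- 5/31 has Wilson limits 0.071 to 0.326, and 0/31 has 0 to 0.110.
- 5/31 against 0/31: difference 0.161. Lower limit 0.161 − √((0.161 − 0.071)² + 0.110²) = 0.019. Upper limit 0.161 + (0.326 − 0.161) = 0.326. In points: +16.1 (1.9 to 32.6).
- 0/31 against 0/31: 0 points (−11.0 to +11.0). Even with no event in either arm, differences of up to about 11 points either way remain possible.
- For one arm alone, 0/31 has an exact two-sided 95% upper limit of 1 − 0.025^(1/31) = 11.2%.

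**The case against.** The strongest reply is that the article never commits to the faulty inference. It does not say that a non-significant p-value will be read as confirming the hypothesis. The hypothesis can be read as an expectation, and Data analysis promises only to classify, tabulate and contrast. A reader might infer that the trial has a decision rule declaring equal safety on non-significance; the text states no such rule. The test is also attached to treatment-emergent adverse events in general, so its use for serious adverse reactions is an inference, though no other between-arm safety comparison is named.

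Two stronger numerical readings also fail. A reader might infer that either named test would pass 0% against 16% as no difference. That is true of Fisher and of Yates-corrected chi-squared, but uncorrected chi-squared rejects it. Nor is non-significance nearly certain whatever the true risk: Fisher's power against 0% is 38% at a true 16.1% and 82% at 25%.

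It can also be said that systematic recording and tabulation of adverse events are already promised, that confidence intervals, the safety population and event definitions are normally left to the SAP, and that this is a phase II trial sized for efficacy. All of this stands, and the difference between the event terms in hypothesis and test is accordingly not pressed as a defect. What remains is that hypothesis and test are both on the page and do not fit. A SAP can add an interval, but without a margin it cannot make a no-difference hypothesis confirmable by a test of difference.

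**Conclusion.** The point holds as a mismatch between a stated primary hypothesis and the only between-arm safety comparison stated. At 31 per arm, Fisher's exact test leaves 0% against 16.1% non-significant (p = 0.053) and has 8% power at true rates of 0% and 10%, and 0.4% at 0% and 5%. The more liberal uncorrected chi-squared reaches 38% and 7%. At low event rates, non-significance is the likely outcome whether or not the arms differ, so it carries little information about equal safety.

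This rests on two-sided testing, on serious adverse reactions being uncommon, and on the named test being the one used for them. It should be fixed, but it is not critical: it does not touch the efficacy inference, and the article does not itself claim that non-significance shows equal safety.

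**What to change.** Replace the no-difference hypothesis with an estimation objective. In substance: to estimate the proportion of participants with a serious adverse reaction in each arm, and the risk difference with its 95% confidence interval. Report the number and proportion per arm with that interval. If a chi-squared or Fisher test is kept, state that a non-significant result will not be interpreted as equal safety.

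If the sponsor wants to keep a claim of no relevant difference, it must state and justify a margin and size the trial for it. For illustration, with one-sided alpha 0.025, 80% power and equal true rates, a 10-point margin needs 31 per arm at a 2% event rate and 75 at 5%; a 5-point margin needs 124 and 299. These margins and rates are assumptions used to show scale, not proposals. Estimation is the realistic course at 62 participants.

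The cost is wording in the protocol and the SAP, with no extra participants, visits or data. The sponsor gives up a no-difference claim that the data could not have supported.
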